### Phase two: qualitative study

2.3

This phase consists of an exploratory qualitative study with conventional content analysis. Using this approach, perceived facilitators and obstacles to adherence to OCR will be investigated and explained.

#### Sampling method

2.3.1

Purposive sampling will be employed to explore patients' perceived facilitators and barriers to adherence to OCR within one month after discharge. Qualitative interviews were conducted after completion of the quantitative phase. Extreme cases on both sides of the overall ACRS score spectrum from phase one (the uppermost and lowermost 10% extreme scores of different subgroups of adherence) will be selected as participants in this phase.

#### Data collection

2.3.2

(1)Gaining access: The researcher will explain the purpose of the study to the directors of the selected hospitals to gain administrative permission and support.(2)Recruiting informants: The researcher will communicate and invite potential informants to participate in the interview. Informants who are willing to participate and available for the time will be interviewed by the researcher. Usually, 20–30 patients of them are invited to participate in interviews. Purposive sampling will be used to recruit informants, some from the high-adherence group and others from the low-adherence group. The interview guide will design questions based on the quantitative study findings before the qualitative phase. The time will be set based on the agreement between the patients and the researcher.(3)Data collection: Digital audio recorders were used during the interviews after obtaining verbal permission. The time for the interview will be 60–90 min.(4)Establishing rapport and trust:
(a)The research coordinator will receive informants with greetings and help them be seated in a quiet private room for the interview in the cardiac clinic and introduce herself to the patients. The research objectives and research questions will be introduced, and patients will be asked to sign an informed consent form.(b)Project posters will be placed to ensure that all informants understand the purposes and procedures.(c)General questions of the informants will be asked before to increase their comfort and level of confidence among them. Then, the interview questions will be gradually raised according to the interview guidelines.

#### Data analysis

2.3.3

Qualitative data will be analyzed using a conventional content analysis approach, which is typically employed with a study design whose goal is to characterize a phenomenon when there is little current theory or research literature on a topic (53). Using this approach, data analysis begins by reading all the data repeatedly to achieve immersion and obtain a sense of the whole. The data were then read word by word to derive codes by first highlighting the exact words from the text to capture critical thoughts or concepts. Next, the researchers make notes of their first impressions, thoughts, and initial analysis. Following this, code labels appear, which are typically the original coding scheme and are frequently taken straight from the text. The researcher selects preliminary codes after open-coding three to four transcripts, which can then be applied to the remaining transcripts. When data do not fit into an existing code, new codes may be added. Consequently, the codes are grouped into categories that make sense. Based on their distinctions and commonalities, these codes are divided into main categories and subcategories. To interpret the underlying meaning, this method makes it possible to extract both manifest content and implicit context (54). The accuracy of the qualitative data will be assessed in this study using traditional criteria (Credibility, Dependability, Confirmability, Transferability) (55). NVivo software (version 12.0) will be employed to manage the interview data.

The “following a thread” method will be used to analyze the data. It begins by analyzing the data of each component to locate important conclusions and unanswered questions. Researchers refer to this as a thread when they take a category or theme from one component and follow it throughout others (56). “Extreme case analysis” is an additional method that involves identifying extreme cases by continuously analyzing datasets. High- and low-extreme cases will be used to demonstrate a substantial association between patients' health perceptions and adherence to OCR.

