#### Sample size and sampling method

2.2.1

According to the suggestion of Nunnally and Bernstien, selecting 5–10 participants per item is appropriate for multivariate analysis (46) 165 participants will be recruited to unitize the factor analysis for the 33 items of the Scale of Adherence to Cardiac Rehabilitation scale (ACRS). Considering a follow-up attrition rate of 20%, this number will increase to 198.

Following the approval of the research project by the Ethics Committee of the two hospitals, the study will be conducted on 198 participants with AMI after PCI one month after discharge who receive home-based OCR. The researchers will visit two hospitals, identify eligible patients using the hospital information system (HIS) following the proportion (70% and 30%) of the target population in two hospitals, explain the study objectives and brief process to them, and obtain informed consent to participate. Patients will complete the Demographic Data Sheet (DDS).

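### Informants chosen from the two ends of the adherence score cannot show that health perceptions and adherence are substantially associated, because that choice exaggerates apparent strength

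*Protocol article*

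**What the plan says.** Section 2.3.1 of the protocol article (Sampling method, phase two) selects informants on the phase-one outcome: "Extreme cases on both sides of the overall ACRS score spectrum from phase one", specified as "the uppermost and lowermost 10% extreme scores of different subgroups of adherence". On numbers, section 2.3.2 says: "Usually, 20–30 patients of them are invited to participate in interviews".

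Section 2.3.3 names extreme case analysis as an additional method and gives it this task: "High- and low-extreme cases will be used to demonstrate a substantial association" between health perceptions and adherence. No caveat about how the cases were chosen accompanies it.

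Two other places bear on how to read that sentence. Section 2.3 gives the purpose of the phase as explanatory: "perceived facilitators and obstacles to adherence to OCR will be investigated and explained". Section 2.2.6 gives the estimation of associations to phase one, through univariate and binary logistic analyses that report odds ratios with 95% confidence intervals.

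**The concern.** To call an association substantial is to make a claim about its size. Dropping the middle 80% of the outcome distribution and contrasting the two ends distorts exactly that. The sentence also settles the result in advance: the cases are there to demonstrate the association, not to examine whether or how it appears.

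The consequence lies in phase three. Section 2.4 sets the main quantitative and qualitative conclusions side by side and puts strategies derived from the earlier phases to an expert panel. If a modest relation looks strong in the interviews and is reported as substantial, strategies aimed at health beliefs could be given more weight than the full sample supports. The interviews are also not independent confirmation, because the informants are phase-one respondents and section 2.3.2 bases the interview guide on the quantitative findings.

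**Working it through.** **Inputs from the article.** Selection of the upper and lower 10% of ACRS (2.3.1); 20–30 informants (2.3.2); phase-one sample of 165 before and 198 after the attrition allowance (2.2.1).

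**Inputs assumed.** The article gives no size for the association, so true correlations r from 0 to 0.30 are used. Adherence and perception scores are taken as bivariate normal.

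**The plan's own figure and the pool it implies.** 33 items × 5 = 165, and 165 × 1.2 = 198, which reproduces the stated sample size. Two 10% tails of 198 hold 2 × 19.8 ≈ 40 patients, or 2 × 16.5 = 33 if 165 remain. The 20–30 informants come from that pool.

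**Spread of the outcome in the tails.** With c = z(0.90) = 1.2816 and normal density φ(c) = 0.1755, the outcome variance in the two tails relative to the full sample is

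k = 1 + c·φ(c)/0.10 = 1 + 1.2816 × 0.1755/0.10 = 3.249, with √k = 1.8025.

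**Apparent correlation in the tails.** r_tails = r·√k / √(1 − r² + k·r²).

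- r = 0.10: 0.18025/1.0112 = 0.178
- r = 0.20: 0.36051/1.0440 = 0.345
- r = 0.30: 0.54076/1.0965 = 0.493

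The correlation is multiplied by about 1.8, 1.7 and 1.6 respectively. Variance explained rises from 4% to 12% at r = 0.20, and from 9% to 24% at r = 0.30. Simulation with 198 patients and 20 + 20 tail cases gave mean correlations of 0.177, 0.345 and 0.495.

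**Effect at interview size, with the number of cases held equal.** Simulated chance of an observed r of at least 0.30 in 25 cases:

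| True r | 25 from the tails | 25 at random |
|---|---|---|
| 0.10 | about 28% | about 16% |
| 0.20 | about 63% | about 31% |

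Comparing 25 tail cases with the whole phase-one sample would give a larger gap, but would mix selection with sample size.

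**No true association.** At r = 0 the mean correlation in the tails is 0.00, and a nominal 5% test rejects in 5.1–5.2% of runs. Selection therefore adds nothing systematic. Chance alone still gives an absolute correlation above 0.3 in about 20% of samples of 20 and about 11% of samples of 30, so this few cases would be weak evidence of existence as well as of size.

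**Slope.** The regression slope of perception on adherence is unchanged by the selection (0.20 stays 0.20; 0.30 stays 0.30). It is the standardised strength that is exaggerated.

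**The case against.** The best defence is that this is one loosely worded sentence in a qualitative section. Phase two uses conventional content analysis and following a thread, and specifies no test, coefficient or p value for the extreme cases. The only statistical analysis of association is the phase-one logistic regression, which uses all respondents and is untouched by the selection. Extreme-case sampling is accepted practice in an explanatory sequential design, and section 2.4 already places the two sets of conclusions side by side.

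Much of this stands. A reader might infer that the selection by itself would manufacture an association; it does not, as the check at r = 0 shows. A reader might also infer that the article plans a second, biased test of the phase-one relation; it describes none. And a reader might expect the extreme cases to be counted as confirming phase one, but section 2.4 does not say so.

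The loose-wording defence does not remove the point. The sentence gives a named method an evidential task about size, departs from the purpose of explaining set out in section 2.3, and feeds the integration without a caveat. If illustration was meant, the text should say so.

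**Conclusion.** The point holds as a minor one. Informants selected from the ends of the outcome score cannot show that the association between health perceptions and adherence is substantial, because that selection makes an existing association look roughly 1.6 to 1.8 times as strong on the correlation scale for true values of 0.10 to 0.30. Since no coefficient is planned for the interviews, this measures how far an impression of strength may mislead, not the bias in a planned estimate.

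The figures rest on normal scores, a linear relation and assumed true correlations. ACRS is bounded at 0–33, so ties or a ceiling would change them. They also rest on reading the 10% rule as the tails of the overall score; the mention of subgroups of adherence could mean tails within each subgroup, which would give other values. The phase-one sample size, outcome and regression are not affected.

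**What to change.** Replace the sentence in section 2.3.3 with wording such as: *Extreme cases will be used to explore and illustrate how and why health perceptions differ between patients with high and low adherence. The existence and size of any association will be taken only from the phase-one analysis of all respondents.* In section 2.4, add that the joint display shows the phase-one estimate with its 95% confidence interval beside the qualitative themes, and that no statement about strength is drawn from the extreme cases.

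Sampling, interviews, instruments and recruitment stay as they are. The one cost is that the interviews can no longer be cited as evidence of how strong the association is.

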### Phase three: integration and development

2.4

Conventional content analysis generally yields an interpretation that offers a comprehensive response to research questions while staying more in line with the phenomenon. Researchers must combine content categories to create a relevant panorama and cogent narrative to accomplish this in practice. It is critical to convey the intricacy of the facts within the larger narrative or interpretation. The key conclusions of both quantitative and qualitative data are presented side by side and narratively reported through “weaving techniques” in data integration. Together, these two sets of data can yield new insights and additional information through joint displays, which offer a deeper and more comprehensive explanation of participant responses and research problems (44).

The nominal group technique (NGT) will be used to develop appropriate strategies to promote adherence to OCR in patients undergoing STEMI-PCI. NGT is a structured group-based technique used to establish a consensus (57). Here's an overview:
•Expert session: We will convene a panel of cardiologists, CR specialists, general practitioners, cardiac nurses, nutritionists, and relevant stakeholders.•Strategy presentation: We will introduce a set of proposed effective strategies derived from earlier research phases.•Input collection: Participants and their families will be invited to provide feedback aimed at refining and prioritizing these strategies.•Synthesis and refinement: The strategies will be further refined based on expert input to ensure they are evidence-based and effective.

## Discussion

3

The main points of lowering the 30-day mortality rate of AMI-PCI patients after discharge and raising patient quality of life are adhering to CR. The causes of non-adherence or low adherence rates, however, are many and complex.

The level and indicators pertaining to adherence to OCR in STEMI-PCI patients should be determined to achieve this goal. This is the first study to examine the level and relevant factors impacting adherence to OCR in STEMI-PCI patents and to design targeted improvement strategies by exploring adherence to OCR using an explanatory sequential mixed-method. This study's design advances our knowledge of the variables that affect OCR adherence by supporting the integration of various viewpoints, strategies, and techniques in line with the principles of epistemological pluralism. To help STEMI-PCI patients achieve better health outcomes, the strategy suggested in this study may help increase awareness among CR providers and policymakers, particularly those pertaining to medical insurance.
